### c. STATISTICAL METHODS TO BE UNDERTAKEN

Analyses will follow a pre-specified statistical analysis plan. The cumulative incidence of PCC following COVID-19 (primary objective) and PAS following influenza will be estimated at 3 months post-infection, with 95% confidence intervals. The proportion of individuals with ongoing symptoms will be reported descriptively (n, %) at 6 and 12 months. The relative risk of developing PCC following COVID-19 versus developing PAS following influenza (objective 2) will be estimated using a log-binomial model. A multivariable logistic model will be developed for predicting PCC at 3 months (objective 3), incorporating pre-specified predictors such as age (treated as continuous), sex, pre-existing conditions, and socioeconomic status. Model performance will be evaluated using the area under the receiver operating characteristic curve, with internal validation by bootstrap resampling in line with TRIPOD recommendations. The relatively small expected number of PCC events may limit the number of predictors that can be incorporated into the final model and hence its predictive accuracy. Linear and negative binomial mixed-effects models will assess differences between comparator groups over time in continuous (PedsQL quality of life and fatigue scores, objectives 4 and 5) and count (days absent, objective 6) outcomes, respectively. Log binomial models will compare the risk of developing PAS according to influenza vaccine uptake (objective 7) and the risk of PCC by COVID-19 reinfection (objective 8). The duration and clinical features of PCC and PAS will be described using summary statistics, with summaries at 3, 6 and 12 months. Descriptive analyses will be based on complete case data.

Handling of follow-up and missing data.

Outcomes will be summarised at the planned 3, 6 and 12-month assessments. Participants contribute data to each analysis for which follow-up information is available. For the primary objective, participants with PCC at 3 months who discontinue or miss assessments at 6 or 12 months will be treated as missing for whether symptoms were ongoing at these time-points. Multiple imputation may be considered for the prediction model, depending on the amount and reasons for missing data at 3 months when determining PCC.

## 9. STORAGE OF BLOOD AND TISSUE SAMPLES

N/A

## 10. DATA SECURITY & HANDLING

### a. DETAILS OF WHERE RECORDS WILL BE KEPT & HOW LONG THEY WILL BE STORED

Data, including consent forms, annual progress reports, recruitment records and study notes, will be kept for 30 years after the research project completion. At completion of the analysis, a de-identified dataset will be stored on the SA Health server, accessible by the PI and SA Health delegate. This de-identified individual patient data (IPD) will also be made available on a case-by-case basis at the discretion of the study team and WCHN HREC. IPD data will only be available to achieve the aims in the approved proposal.

A separate list of participant's study ID, first names, last names, and dates of birth will be encrypted, password-locked and saved in a Vaccinology and Immunology Research Trials Unit (VIRTU) folder on the SA Health server. Accessible by the PI and SA Health delegate. The original database with identifiable data will be encrypted, password locked, stored on a SA Health server, and deleted from the REDCap after the analysis.

### b. CONFIDENTIALITY AND SECURITY

In phase 1 of the study, basic baseline information of all COVID-19 and influenza cases presenting to a WCHN site will be collected by a WCHN employed level 2 Registered Nurse from EMR to provide baseline denominator data for those not enrolled in the study. Any identifiable information obtained from WCHN eligible cases will not be provided to non-WCH members of the study team without the participant's consent.

In phase 2 of the study, SA Health notifications will be used to identify potential participants. The SA Health Centre for Disease Control Branch (CDCB) utilises an existing SMS platform to manage the sending of invitations and provide access to the information sheet and consent form. Only aggregated non-identifiable data will be provided by CDCB to the study team for those who do not provide consent, as per Figure 3. Identifiable data from individuals contacted based on SA Health notifications will be provided to the study team only after they have given informed consent.

RedCap sits within the Central Adelaide Health Network Digital Health World and cannot be accessed outside the SA Health network. It is encrypted and password-protected.

For those that consent, the baseline, 3, 6, and 12 months survey data will be collected using a secure RedCap database stored on a SA Health server (CALHN), behind a SA Health firewall. The database will only be able to be accessed by designated study staff, who are employees of SA Health. Data will only be able to be extracted by the study PI, and no identifiable data will be stored outside of the password-protected RedCap database. The final dataset will be de-identified before being stored securely on a SA Health computer, only accessible to study staff. Information published from this study will not identify any participants involved in this study.

### c. ANCILLARY DATA

N/A

## APPENDIX A DISTRESS PROTOCOL

### Introduction

This distress protocol is designed to ensure the safety and well-being of participants in our study, which includes sensitive questions on quality of life. Although such protocols are common in qualitative research, our study's inclusion of physical and mental health topics, school or work absenteeism, healthcare visits, and detailed quality of life assessments from the PedsQL questionnaires presents a minor risk of emotional distress to participants and their parents.

### Managing Distress and Providing Support

To provide for a child and young person's safety, emotional and psychological security, and well-being, our approach includes:

- **Participant Information:** An information sheet that outlines the study's aims, potential emotional risks, and participant's rights.
- **Support Resources:** At the end of each survey, participants have information to access to a variety of support options:
  1. Contacts for 24/7 Mental Health Services (e.g., Beyond Blue, Kids Helpline for ages 5-25) for access to immediate counselling.
  2. Contact information for the 24/7 Healthdirect on-call service for after-hours health advice.
  3. A recommendation to see their regular GP for non-urgent health concerns.
  4. An email contact for a Registered Nurse from the study team for any study-related questions or issues.
- **Follow-Up Procedures:** Participants with quality of life scores below established thresholds, who have not previously sought healthcare advice, will be considered for telehealth contact (Appendix B). This step ensures they have the necessary support and offers additional help based on their personal needs and choices.
- **Feedback Mechanism:** At the end of each survey, participants will be given a free text option to give feedback on the survey process, including anything they found challenging. This feedback will enable continuous improvement of our survey questions and distress protocol.
- **Participant Autonomy:**
  1. At the start of each survey, participants are informed that they can skip any question they prefer not to answer.
  2. Participants are reminded that they retain the right to withdraw from the study at any stage, as outlined in the information sheet and within the survey instructions.
- **Experience of Researchers:**

An experienced level 2 registered nurse with over 20 years of clinical and 10 years of research experience will handle the participants' queries and review the surveys. When required, advice will be sought from study team members, including paediatricians and child psychiatrist.

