### b. HANDLING OF WITHDRAWALS

Participants may withdraw from the project at any time and refuse to answer any survey questions. They can withdraw by contacting the study team via email or phone and indicate if they wish to withdraw all their data from the study, future contact, or just future surveys. The REDCap database will have a variable that allows the PI to add the type of withdrawal and stop future automatic surveys from being sent out. The REDCap survey will also have the option to withdraw from the study within the questionnaire.

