## APPENDIX B FOLLOW-UP OF ONGOING SYMPTOMS PROCESS

### Introduction

After participants complete the survey, a registered nurse or Paediatrician will review the responses to ensure that individuals with ongoing symptoms from COVID-19 or influenza are identified for further medical evaluation and care. This review assesses participants' health status and engagement with healthcare services to determine if a referral to a healthcare provider is necessary.

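### Support contacts are placed at the end of each survey, so a respondent who uses the in-survey withdrawal option does not reach them

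*Protocol*

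**What the plan says.** Appendix A (Managing Distress and Providing Support) lists four contacts: round-the-clock mental health services, the national health advice line, the family's GP and an email address for a study nurse. It fixes where they appear: "At the end of each survey, participants have information to access to a variety of support options". The same list puts a different notice at the beginning: "At the start of each survey, participants are informed that they can skip any question they prefer not to answer". It also reminds participants that they may withdraw at any stage.

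Section 7.b gives two ways out. One is outside the survey: "They can withdraw by contacting the study team via email or phone". The other is inside it: "The REDCap survey will also have the option to withdraw from the study within the questionnaire". It also distinguishes withdrawing all data, declining future contact and declining only future surveys.

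On reviewing answers, the Appendix B introduction says: "After participants complete the survey, a registered nurse or Paediatrician will review the responses". Appendix A says of the study nurse that this person "will handle the participants' queries and review the surveys", with no mention of completion. Section 5.b and the telehealth criteria in Appendix B commit to contacting those who report severe symptoms and have not been medically assessed, again with no mention of completion.

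**The concern.** Section 7.a names distress caused by the questions as a risk and points to Appendix A as the mitigation. It names missed untreated symptoms as another and points to Appendix B. Stopping early is a foreseeable reaction to an upsetting question, and the protocol builds an exit for it into the questionnaire. If the contacts sit on the last page, that exit leads away from them. The person the list is meant for may then be the one who does not see it on that occasion.

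A second, separate issue is clarity. If the review is read as starting only on completion, staff have no stated rule for answers saved before someone stopped. Two staff members could act differently on the same record. What is at stake is participant support and consistent conduct, not the validity of any estimate.

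**Working it through.** No arithmetic applies, and the protocol has no figure of its own to reproduce. The check sets the provisions side by side.

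**1. Position of the contacts.** Appendix A uses two positions in the survey. The skip notice comes at the start. The contacts and the free-text feedback box come at the end. Because the appendix distinguishes the two, the end position reads as a choice and not as loose wording.

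**2. Exit routes.** Section 7.b provides withdrawal within the questionnaire. Appendix A confirms withdrawal at any stage. Neither links the withdrawal step to the contact list. Section 5.c provides two reminders, a week apart, when a survey gets no response, and no step for one that was started and left.

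**3. Steps 1 and 2 together.** A respondent who withdraws or stops before the last page does not reach the list in that survey.

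**4. Who has no earlier list to fall back on.**
- *First survey.* Nobody has yet reached an end page. Table 1 marks physical and mental health symptoms at baseline, so sensitive content is already present. The PedsQL scales start at 3 months.
- *Change of respondent.* Section 5.c lets 12- to 18-year-olds complete surveys themselves where a parent judges them mature enough. The data lists record who filled in each questionnaire, at baseline and at follow-up. An adolescent may therefore meet the quality-of-life items having never seen the end page that a parent reached at baseline.
- *Same respondent, earlier survey completed.* This person has already been given the contacts, and the gap is small.

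**5. Review of answers.**

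| Place | Tied to completion? |
|---|---|
| Appendix B, introduction | Yes: review follows completion |
| Appendix A, experience of researchers | No: the nurse reviews the surveys |
| Section 5.b | No: all children reporting severe persistent symptoms not yet assessed |
| Appendix B, telehealth criteria | No: severe symptoms identified through the survey |

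One statement is tied to completion and three are not. The text does not say that saved partial answers go unreviewed, nor that they are reviewed. It can be read either way.

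**The case against.** The best case for the protocol is that it is silent on part-completed surveys and does not actually fail them. Placing contacts at the end of each survey does not say they appear nowhere else. The skip notice lets a distressed respondent pass over questions and still reach the end page. The study team can be reached by email or phone, although Section 7.b describes this for withdrawal. Appendix A also lists this: "An information sheet that outlines the study's aims, potential emotional risks, and participant's rights". It calls the distress risk minor. Most of this stands and limits the size of the point. It does not remove it: skipping helps those who continue, while the gap concerns those who use the exit the protocol offers.

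A reader might infer more, and the documents do not support it:

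- *That both safeguards fail for anyone who stops early.* A respondent who finished an earlier survey already has the contacts. Appendix B screens for severe symptoms and low PedsQL scores; it does not detect distress caused by the survey.
- *That severe symptoms already entered are not reviewed.* Three of the four statements on follow-up carry no completion condition, and the fourth may describe only the usual timing.
- *That a partial survey enters the analysis but escapes review.* Section 8.c says: "Participants contribute data to each analysis for which follow-up information is available". In context this concerns which of the 3-, 6- and 12-month assessments are available, not half-finished questionnaires.
- *That the information sheet lacks the contacts.* The sheet is not among the pages available, and a one-line summary cannot show what it omits.
- *That the number of families affected can be calculated.* The protocol gives no rate of part-way stopping. Any assumed rate would also count stops for interruption or loss of interest, and follow-up surveys come after a baseline survey with its own end page.

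**Conclusion.** The point holds in a narrow form. As the protocol is written, the in-survey exit bypasses the page on which Appendix A places the support contacts. This matters most in a first survey and for an adolescent who takes over from a parent. The Appendix B introduction also needs to be aligned with Section 5.b, Appendix A and the telehealth criteria, so that saved answers in a part-completed survey are handled in one stated way.

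This is a minor safeguarding improvement, with no effect on the incidence estimates, the comparisons or the sample size. It rests on two assumptions: that the survey is built as Appendix A describes, and that the withdrawal step does not already show the list. If the survey as built already shows it there, only the text needs correcting.

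**What to change.** 1. In Appendix A, state that the existing support list, unchanged in content, is also shown at the start of each survey and on the in-survey withdrawal page, as well as at the end. Showing it at the start also covers a respondent who simply closes the survey.
2. Reconcile the Appendix B introduction with Section 5.b, the nurse-review statement in Appendix A and the telehealth criteria in Appendix B. The text should say unambiguously how responses saved in a part-completed survey are handled. Leave the symptom triggers and PedsQL cut-offs as they are, and make the handling subject to the withdrawal type chosen under Section 7.b.

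The cost is minor survey-page configuration and a few sentences of protocol text. No outcome, schedule or analysis changes.

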## APPENDIX B FOLLOW-UP OF ONGOING SYMPTOMS PROCESS

### Introduction

After participants complete the survey, a registered nurse or Paediatrician will review the responses to ensure that individuals with ongoing symptoms from COVID-19 or influenza are identified for further medical evaluation and care. This review assesses participants' health status and engagement with healthcare services to determine if a referral to a healthcare provider is necessary.

### Telehealth Review Process

#### Identification of Participants for Telehealth Contact with Severe Symptoms:

Participants describing severe ongoing symptoms identified through the survey and not yet assessed by a medical professional (asked in the survey) will be contacted for a telehealth review. The following symptoms, among others, will prompt a follow-up:

- Constant headaches
- Difficulty breathing
- Chest pain
- Palpitations, high pulse, or irregular heartbeat
- Constant dizziness
- Problems with swallowing or chewing
- Seizures or fits
- Impaired movement control
- Speech and language difficulties
- Vision problems or blurred vision
- New allergies

#### Identification of Participants for Telehealth Contact Based on PedsQL Scores:

Participants with PedsQL scores below established clinically meaningful cutoffs will be considered for telehealth contact if they have not previously sought healthcare consultation for their symptoms or reported a pre-existing condition. The cutoff scores are:

### Child Self-Assessment

- Physical Functioning: 73
- Emotional Functioning: 60
- Social Functioning: 67
- School Functioning: 63

### Parent Assessment

- Physical Functioning: 63
- Emotional Functioning: 63
- Social Functioning: 62
- School Functioning: 57

